### Intervention

Participants in both groups will receive conventional neurorehabilitation–treatment as usual. This comprises of 45 min physiotherapy sessions 5–7 times per week individual or in groups. Treatment’s focus depends on individually set goals agreed upon in the rehabilitation plan. The intervention group will receive add-on IMT sessions with exercises at 30% of MIP. MIP is measured by instructing the patient to perform five forceful inspirations against an occluded mouthpiece Power Breathe KH2 (POWERbreathe International Ltd, UK). The best score is multiplied by 0.3 to determine resistance. IMT is performed with the Threshold IMT (Philips, UK) with the calculated resistance. During the Power Breath measurement, the patient sits straight up and uses a nose clip. The patient may receive help to hold the Power Breath if necessary.

One session of IMT with the Threshold IMT consists of two times 15 inspirations at normal breathing rhythm (5–10 min). Patients in the intervention group perform two sessions a day (morning and evening); training is performed prior to a meal, 7 days a week for 3 weeks. According to the patients’ need of support, IMT can be with or without supervision. MIP is reassessed every 7 days, and a new resistance is calculated. Patients in the intervention group log their IMT in a log book. The log book supports the patient in performing the right number of respirations twice a day for 3 weeks. The patient sits straight up in a chair/wheelchair/armchair, possibly with a table in front of him or her during practice. The Threshold IMT mouthpiece is placed after the resistance has been set manually. The nose clip must be used during practice to ensure that air passes through the mouth only. Any adverse events are noted in the log book and the staff will contact the project manager. The project manager will in collaboration with the patient and the physiotherapist decide what action to take. As inpatients, the participants in this project are covered by patients’ right to apply for compensation if any unexpected events related to IMT should occur.

### Outcomes

The primary outcome measure is MIP assessed by Power Breath [18]. This is an objective measurement used to describe the inspiratory capacity.

Secondary outcome measures include the following: the Functional Independence Measure (FIM) to assess the degree of dependency in daily activities—both total score and motor sub score [19]—and the 6-min walking test to measure endurance [20–22]. Fatigue was measured by the Fatigue Severity Scale [23, 24]. Average voice volume will be measured by recording of an a-sound with the app Voice Analyst. Phonation endurance (how long the a-sound lasts) is noted. The patient tries three times, and the average is then calculated. Expiratory function is as follows: peak expiratory flow (PEF), forced expiratory volume in 1 s (FEV1), forced vital capacity (FVC) and FEV1/FVC ratio will be assessed with Spirometry device (Vitalograph Micro 6300, Ireland). All respiratory measures are performed in sitting position. The patient tries three times. Subsequently, the best score is used for further analysis [12].

### Test procedure

All assessments will be conducted at baseline, 3 weeks (at termination of the intervention) and 3 months after the intervention concluded. The Patient Global Impression of Change (PGIC) scale will be employed upon conclusion of the intervention [25].

Outcome assessors are blinded to the intervention. Testing takes place in a specific room at the recruitment hospital. Outcome assessors are physiotherapists trained in performing the test procedures and are not joining the treatment team at the recruiting ward. Patients will be tested by the same therapist all three times. The trial participants and intervention providers are not blinded.

### Sample size

Power was calculated to establish the needed number of participants. The power calculation was based partly on a local pre-study (including 26 patients) and on a RCT study [12], which showed differences in variance in ∆MIP assessments. ∆MIP is defined as (MIP at 3 months minus MIP at baseline). Because of the difference in variances in the intervention group and the control group, the same power can be achieved by distributing them unequally between the groups. It is assumed that the standard deviation is three times larger in the intervention group than in the control group. The power calculation prescribes 20 patients in the control group and 60 patients in the intervention group. Calculations were made, expecting a 10% dropout. The least clinically relevant difference was estimated to 5 cmH_2_O.

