### Objectives

The two primary objectives of this study are to investigate:
The effect of 3 weeks of IMT on maximal inspiratory pressure (MIP) in adults having suffered stroke.The effects of 3 weeks of IMT on the degree of dependency in activities of daily living, endurance in gait, fatigue, voice volume (VV), phonation endurance (PE) and expiratory function; peak expiratory flow (PEF), forced expiratory volume in 1 second (FEV1), forced vital capacity (FVC) and FEV1/FVC ratio.

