### Statistical analysis

Data will be analysed as intention-to-treat and per protocol. Between-group differences (3-month follow-up minus baseline) are compared by the *T* test. Regression analysis is conducted with adjustment for the confounders’ age and time from stroke to baseline assessment.

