## Discussion

The primary purpose of this study is to assess the effect of an IMT intervention in patients with reduced MIP following stroke. A secondary purpose is to assess the effect of IMT on the degree of dependency in activities of daily living, endurance in gait, fatigue, voice volume, phonation endurance and expiratory capacity. Hereby, this study accepts the call for further research made by Xiao [9].

The study assumes that by strengthening the diaphragm muscle and the intercostal muscles, patients will gain faster respiratory recovery, which, in turn, will allow them to practice or carry out activities of daily living earlier in the course of their rehabilitation. The typical length of IMT interventions is 6–8 weeks [12, 13, 26]. In 2019, the average hospitalisation in the study setting for stroke patients was 34 days (95% CI 21–52 days). The length of the intervention was set to 21 days to ensure that the intervention could be completed during hospitalisation. The duration of the intervention was also informed by positive results from the pre-study. We argue that it is interesting to investigate whether or not a shorter intervention period is sufficient for patients to experience a positive impact on MIP and the degree of their dependency in activities of daily living, endurance in gait, fatigue, voice volume, phonation endurance and expiratory function*.* Especially, we find it valuable to investigate the effect of increasing intensity in rehabilitation as the intervention is relatively easy and inexpensive to implement and may be practiced by many patients on their own as an add-on to their rehabilitation.

A broad spectrum of patients with sensorimotor deficits following stroke is expected to be included in the study, as it does not exclude patients based on the severity of their stroke. We find it important to develop interventions that may also have an impact on the more severely injured patients.

Sham IMT was considered for the control group, but was rejected for ethical reasons, as it would be time consuming for patients to do the sham intervention, which would be unethical as these patients need to economise their resources due to fatigue.

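### Only the 3-month change in MIP is powered and tested; the end-of-training assessment has no stated between-group analysis, and the Objectives section labels secondary endpoints as primary

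*Protocol article*

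**What the plan says.** **Time point.** Sample size defines the MIP change as "MIP at 3 months minus MIP at baseline". Statistical analysis then states: "Between-group differences (3-month follow-up minus baseline) are compared by" the T test. The only other analysis named is a regression adjusted for age and time since stroke: "Regression analysis is conducted with adjustment for the confounders"; it gives no time point.

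**Assessments.** Test procedure sets three visits: "All assessments will be conducted at baseline, 3 weeks (at termination of the intervention) and 3 months after the intervention concluded". The Abstract and the Design section agree; Design places the second visit 0–4 days after training ends.

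**Purpose.** The first objective is "The effect of 3 weeks of IMT on maximal inspiratory pressure (MIP) in adults having suffered stroke". The title speaks of faster recovery. The Discussion assumes that "patients will gain faster respiratory recovery, which, in turn, will allow them to practice or carry out activities of daily living earlier", and it asks whether a course shorter than the usual 6–8 weeks is enough.

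**Hierarchy of endpoints.** Objectives opens with "The two primary objectives of this study are to investigate", and its second item lists dependency, gait endurance, fatigue, voice, phonation and expiratory measures. Outcomes names MIP as the primary outcome and the rest as secondary. The Discussion likewise separates a primary purpose (the effect in patients with reduced MIP) from a secondary one (the other endpoints).

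**The concern.** Training stops at 3 weeks, and patients enter within 3 months of a stroke, when controls may still be improving on their own. A single contrast about three months after training ends can show whether a benefit lasts. It cannot show whether patients improved sooner. If that contrast is null, the stated analysis alone does not distinguish a treatment that did nothing from one whose benefit faded or was matched later by the controls. The visit that could help tell these apart is already in the schedule but has no stated comparison. If its analysis is settled only after results by arm are known, the choice between two time points is open to selection.

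A two-point change score also needs both values. Unless missing 3-month values are imputed, a patient with a baseline and a 3-week MIP but no 3-month MIP contributes nothing.

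The label in Objectives is a separate matter. Taken at its word, it would let a positive result on any of about ten further endpoints be presented as a primary finding.

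**Working it through.** **1. Can the plan's own sample size be reproduced?** Only in part.

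- Inputs from Sample size: difference 5 cmH2O, SD in the IMT arm three times that in controls, 60 IMT and 20 control patients, 10% dropout.
- Not stated in the article: the SDs, alpha, sidedness and power.
- Dropout: 80 × 0.90 = 72 evaluable, that is 54 and 18, and 72 / 0.90 = 80. This is consistent.
- Implied SDs, assuming two-sided alpha 0.05, 80% power and a normal approximation: SE = SDc × √(1/18 + 9/54) = 0.4714 × SDc. Setting 5 / SE = 1.960 + 0.842 = 2.802 gives SE = 1.785, so SDc = 3.79 and the IMT SD = 11.36. At 90% power the SDs are 3.27 and 9.82.

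The figure of 80 can therefore be neither confirmed nor refuted. The point made here does not depend on it.

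**2. Where does each visit enter the stated analysis?**

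| Visit | Assessed | In the power calculation | In a named between-group test |
|---|---|---|---|
| Baseline | yes | yes | yes |
| 3 weeks | yes | no | no |
| 3 months | yes | yes | yes |

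The regression could be applied to either follow-up visit, because no time point is given for it.

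**3. What could be lost if an early effect fades? (Illustration.)** Suppose the effect is 5 cmH2O at 3 weeks, a fraction r remains at 3 months, and the SDs are the same at both visits. Power of the 3-month test = Φ(r × 5 / SE − 1.960).

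| r | From an assumed 80% | From an assumed 90% |
|---|---|---|
| 1.00 | 80% | 90% |
| 0.75 | Φ(2.101 − 1.960) = 55.6% | 68.1% |
| 0.50 | Φ(1.401 − 1.960) = 28.8% | 36.7% |

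The values of r are assumptions; the protocol gives no information on fading or persistence.

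**4. Unused values.** The planned dropout is 10% of 80 = 8 patients. At most that many would lack a 3-month value under the protocol's own expectation. How many of them would have a 3-week MIP is not stated.

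**5. Endpoints under the two labels.** The second objective lists nine endpoints. Outcomes splits FIM into total and motor scores, which makes ten, and MIP makes eleven. If eleven independent tests were each run at 5%, the chance of at least one false positive would be 1 − 0.95^11 = 43%. The endpoints are not independent: the FIM motor score is part of the total, and FEV1, FVC and their ratio are linked. The 43% is thus a reference value only.

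**6. Would testing both time points as primary be affordable?** With Bonferroni at 0.025 each, power per test falls from 80% to 71.2%, and restoring it needs about 88 evaluable patients instead of 72. One primary contrast with the other as key secondary avoids this.

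**The case against.** The strongest reply is that 3 weeks, in the first objective, is the length of training and not an assessment time. A reader might infer that the trial's own question goes untested. The documents do not support that: a randomised comparison at 3 months does test an effect of 3 weeks of IMT, namely a lasting one, and this is a legitimate primary target. Faster recovery stands in the title and the rationale, not in the listed objectives. This stands.

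Second, the article condenses a fuller plan. A reader might infer that the 3-week data will never be analysed, or that patients without a 3-month value will be excluded in breach of the stated intention-to-treat analysis. Neither is stated. The regression has no time point, and the handling of secondary visits and missing values may be set out elsewhere. This stands too, and it limits the point to what the article fixes: one powered and tested time point, with a change-score T test.

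Third, a reader might conclude that the primary time point should move to 3 weeks. Enrolment began on 1 February 2021 and this protocol version is dated 16 August 2021. Project management sees allocations after randomisation, and the Steering Committee discusses interim results. A change of primary time point during recruitment could look driven by data, and no 3-week SD is given from which to restate power. The objection is sound, and the fix keeps 3 months as primary.

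Fourth, the label in Objectives may be a slip, since Outcomes names one primary outcome and only MIP is powered. That is likely, but the contradiction remains in the text.

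**Conclusion.** The point holds as a low-cost improvement and not as a flaw that invalidates the design. The protocol powers and tests a sustained effect on MIP at 3 months. It states no between-group analysis of the end-of-training visit, so the stated analysis does not address the immediate effect or the speed of recovery. The change-score T test is also less efficient than the data allow: unless values are imputed, it passes over 3-week MIP from patients who miss the last visit.

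The contradiction over which endpoints are primary is plain from the text and rests on no assumption.

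The sizes are conditional. The fall in power to about 56% or 29% assumes 80% power for 5 cmH2O at 3 weeks, two-sided alpha 0.05, 54 and 18 evaluable patients, equal SDs at both visits, and a fade of 25% or 50%. The 43% assumes eleven independent tests. The documents state none of the power, alpha, SDs, fade or independence, so these figures show direction and scale and do not forecast the trial's result.

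**What to change.** 1. Keep the 3-month contrast, on which the sample size rests, as primary and say why it was chosen. If the sponsor prefers another time point, the change must be justified and recorded before anyone sees data by arm, and power must be restated for it.
2. Replace the change-score T test with one longitudinal model of MIP at 3 weeks and 3 months. Include arm, visit, arm-by-visit and baseline MIP, let the variances differ by arm (the sample size itself assumes a threefold SD ratio), and include every randomised patient with any post-baseline MIP. The planned covariates, age and time since stroke, can enter the same model.
3. Pre-specify the 3-week contrast from that model as the key secondary result, so that an early effect that fades can be told apart from no effect.
4. In Objectives, keep MIP as the only primary objective and relabel the second as secondary, in line with Outcomes and Discussion.

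The cost is slightly more analysis work and an update of the protocol and registry wording. No extra patients, visits or measurements are needed while a single contrast stays primary.

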### Statistical analysis

Data will be analysed as intention-to-treat and per protocol. Between-group differences (3-month follow-up minus baseline) are compared by the *T* test. Regression analysis is conducted with adjustment for the confounders’ age and time from stroke to baseline assessment.

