### Randomisation

An independently controlled, computer generated randomisation will be implemented in REDCap [16, 17] by an externally based datamanager. The allocation will be concealed to the involved assessors. Only the project management has access to the randomisation information in REDCap and only after each patient has been randomised. The project manager informs the physiotherapist at the ward about the allocation. Afterwards, the physiotherapist informs the patient. A stratified block randomisation of severity of impairment based on Modified Rankin Scale (mRS) (< 4) and a block size of 4 with an intervention/control ratio of 1/3 will be performed. Furthermore, a stratification on the two participating neurorehabilitation units will be performed.

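### The T test and regression for change in MIP make no stated allowance for the threefold SD difference behind the 60/20 split; the usual equal-variance forms would forfeit much of the planned power

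*Protocol article*

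**What the plan says.** The Sample size section of the protocol article defines change in MIP as the 3-month value minus baseline and makes this assumption about its spread: "It is assumed that the standard deviation is three times larger in the intervention group than in the control group". It gives the same feature as the reason for unequal arms ("Because of the difference in variances in the intervention group and the control group", the same power can be reached with an unequal split) and concludes: "The power calculation prescribes 20 patients in the control group and 60 patients in the intervention group". The target difference is 5 cmH2O ("The least clinically relevant difference was estimated to 5 cmH_2_O"), and dropout is allowed for: "Calculations were made, expecting a 10% dropout". Alpha, sidedness, target power and absolute SDs are not given.

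The Statistical analysis section takes the same variable: "Between-group differences (3-month follow-up minus baseline) are compared by the" T test. It adds: "Regression analysis is conducted with adjustment for the" confounders age and time from stroke to baseline assessment. It does not say whether the T test is the pooled or the unequal-variance form, or how the residual variance of the regression is estimated.

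**The concern.** A threefold SD ratio is a ninefold variance ratio, and it is the only reason given for a 60/20 design. A T test named without qualification is commonly taken as Student's equal-variance test, and a regression named without qualification as one with a single residual variance. Both rest on the condition that the Sample size section assumes to be false.

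Equal arms would largely hide the mismatch. With a 3:1 split they do not: the pooled variance is weighted towards the large, noisy arm and is then applied to the small, quiet arm as well. The standard error comes out too large, so a real 5 cmH2O difference could be missed in a trial that was sized to find it. If the form is left open until the data are seen, two defensible readings of the same sentence could also give different primary conclusions.

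**Working it through.** **Inputs from the Sample size section.** Intervention SD = 3 × control SD (write the control SD as s); 60 intervention and 20 control patients; 10% dropout; difference 5 cmH2O. **Assumed, because not stated:** two-sided alpha 5%; target power 80% or 90%; normal data.

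**1. The plan's own figures.** The total of 80 cannot be reproduced without alpha, power and an absolute SD. The split can: the allocation that minimises the variance of the difference has n_I/n_C = SD_I/SD_C = 3, which gives 60/20. For dropout, 60 × 0.9 = 54 and 20 × 0.9 = 18. So the split is the optimal one for an analysis that allows the variances to differ.

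**2. Standard error at 60/20, in units of s.** This step needs no assumption beyond the SD ratio.
- True SE: √(9/60 + 1/20) = √0.200 = 0.447.
- Pooled variance: (59 × 9 + 19 × 1)/78 = 550/78 = 7.05.
- Pooled SE: √(7.05 × (1/60 + 1/20)) = √0.470 = 0.686.
- Ratio: 0.686/0.447 = 1.53, so 53% too wide.

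For comparison, 40/40 has SE √(9/40 + 1/40) = 0.500, and there the pooled formula gives the same value. Under a pooled analysis, the 60/20 split would therefore report a wider SE than equal arms would.

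**3. Type I error at 60/20, two-sided 5%** (400,000 simulated data sets per setting):

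| SD ratio | Equal-variance | Welch |
|---|---|---|
| 1 | 5.0% | 5.0% |
| 1.5 | 1.8% | 5.0% |
| 2 | 0.8% | 5.0% |
| 3 | 0.3% | 5.0% |

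**4. Power at 54/18.** True SE = s√(9/54 + 1/18) = 0.471s. The SDs are back-solved from 5/(0.471s) = 1.960 + z(power):
- 80%: s = 5/(2.802 × 0.471) = 3.79, so the intervention SD is 11.36.
- 90%: s = 5/(3.242 × 0.471) = 3.27, so the intervention SD is 9.82.

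| Planned power | Equal-variance | Welch |
|---|---|---|
| 80% | 40.7% | 78.8% |
| 90% | 57.4% | 89.2% |

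A hand check agrees. The pooled/true SE ratio at 54/18 is 1.534 and the critical t on 70 df is 1.994, so the estimate must exceed 1.994 × 1.534 = 3.06 true SEs. Φ(2.80 − 3.06) is about 40%, and Φ(3.24 − 3.06) is about 57%. If the SDs are instead solved at 60/20 without dropout, the results are the same (about 41% against 79% on an 80% plan).

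On the 80% plan, the pooled test would need about 102 + 34 evaluable patients to reach 79%.

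**5. Regression with two covariates at 54/18, 80% plan** (4,000 simulations). With one residual variance: type I error 0.45%, power 39%. With HC3 standard errors: type I error 4.0%, power 72%.

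**The case against.** The strongest reply is that the text never says pooled. A Welch test is a T test, and the regression is not described as having one common variance. The authors plainly knew that the variances differ, and the analysis plan or full protocol, which is not shown, may name the form. This stands as far as it goes: the defect is an unstated variance form, and every figure above on the equal-variance test is conditional on that form being used. It does not remove the point. The article is not silent on the analysis; it names a test whose unqualified name usually carries the very assumption that the sample size denies.

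The type I figures also assume that the ratio of 3 persists when there is no effect. If the extra spread comes from varied response to training, the SDs might be equal under the null, and the pooled test would then hold 5%. The ratio itself is a planning value, based partly on a 26-patient pre-study, which the Discussion describes as having had no control group. Both remarks are fair. The loss of power arises when there is an effect, which is where the plan's ratio is meant to apply.

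A reader might infer that the plan risks false positives. With the noisier arm the larger one, the pooled test errs the other way. Inflation to about 21% would arise only if the ratio in the Randomisation section ("a block size of 4 with an intervention/control ratio of 1/3 will be performed") were applied literally, putting 20 patients in the intervention arm and 60 in the control arm. That contradicts the Sample size section and must be reconciled separately. Welch would hold 5% there but would not restore power (about 41% at 18/54 on the 80% plan).

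**Conclusion.** The point holds in conditional form. The plan sizes the arms on a threefold SD difference in change in MIP, then names a T test and a regression for that variable without allowing for it. The 53% excess in the standard error follows from the stated SD ratio and arm sizes alone, if the pooled form is used. The type I error of about 0.3% also assumes a two-sided 5% test. The power figures (about 41% against 79%, or 57% against 89%) further assume the target power, with SDs solved from it. At SD ratios between 1 and 3 the distortion is smaller but in the same direction, and at ratio 1 it disappears.

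The documents do not support the stronger statement that the standard error, type I error and power are wrong as planned, because the variance form is left open. Under the Sample size section's allocation, the consequence is a conservative test with over-wide intervals and a substantial loss of power.

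**What to change.** In the Statistical analysis section, state that change in MIP is compared by the Welch (Satterthwaite, unequal-variance) t test, and that the adjusted regression uses arm-specific residual variances or heteroscedasticity-consistent (HC3) standard errors. Settle this before any unblinded analysis.

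The cost is one sentence. If the variances prove equal, the loss is negligible. HC3 is slightly conservative at these sizes (72% power on an 80% plan), but keeps far more power than the single-variance regression. Extending the rule to the other continuous outcomes is optional, since the SD ratio is stated only for change in MIP.

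### The stated T test on 3-month-minus-baseline MIP has no value for patients without a 3-month MIP, so on observed data it would be a completer analysis and not the promised intention-to-treat analysis

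*Protocol article*

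**What the plan says.** Protocol article, Statistical analysis: "Data will be analysed as intention-to-treat and per protocol". The next sentence names the comparison: "Between-group differences (3-month follow-up minus baseline) are compared by the" T test. A third adds a covariate-adjusted model: "Regression analysis is conducted with adjustment for the confounders" age and time from stroke to baseline.

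The Sample size section defines the outcome by the same two time points, "MIP is defined as (MIP at 3 months minus MIP at baseline", and says of attrition: "Calculations were made, expecting a 10% dropout". It also states: "The power calculation prescribes 20 patients in the control group and 60 patients in the intervention group".

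Under Test procedure, every assessment is scheduled at baseline, at 3 weeks and 3 months after the intervention, and "Testing takes place in a specific room at the recruitment hospital". The Data monitoring section says that missing data will be chased during collection. The article does not say how a patient whose 3-month MIP stays missing enters the analysis.

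**The concern.** Intention-to-treat normally means that every randomised patient contributes to the comparison in the arm assigned. A two-sample T test on a change score, or a regression on it, can use only patients with both values. For the patients whom the plan itself expects to lose, the label and the named method do not fit together unless some further step is taken, and the article names none.

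Loss need not be random. The Discussion gives an average stay of 34 days, while the endpoint falls 3 months after a 3-week intervention. Many patients would therefore have to return to the hospital after discharge, in a trial that deliberately takes severely affected patients. If return depends on how a patient has done, the completer contrast can be biased. The plan's assumption of a threefold SD in the IMT arm matters here: the same dropout pattern, expressed in SD units, shifts the IMT mean three times as far as the control mean, so the shifts do not cancel.

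The 3-week MIP carries information about patients who leave later, and the stated analysis makes no use of it.

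**Working it through.** **Numbers analysed.** From Sample size: 60 IMT, 20 control, 10% dropout. 80 × 0.9 = 72; if dropout is equal by arm (an assumption, since no split is given), 60 × 0.9 = 54 and 20 × 0.9 = 18. This is a planning expectation, not an analysis set that the article defines.

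**Plan's own figure.** The total of 80 cannot be reproduced, because alpha, sidedness, power and absolute SDs are not stated. Solving backwards from 5 = (z_alpha + z_power) × √((3s)²/54 + s²/18), two-sided 5%, gives SDs of 3.8 (control) and 11.4 (IMT) at 80% power, or 3.3 and 9.8 at 90%. I assume 3.73 and 11.2, close to the first pair.

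**General form of the bias.** Let p be the share missing and g the completer mean minus the dropout mean of change. Then bias = p_IMT × g_IMT − p_ctrl × g_ctrl. With 10% missing in both arms:

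- g equal in cmH2O in both arms: 0.
- g = 5 to 10 in the IMT arm only: +0.5 to +1.0.
- g = 5 to 10 in the control arm only: −0.5 to −1.0.

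If all 8 dropouts are in the IMT arm (8/60 = 13.3%) and g = 5 to 10, the bias is +0.7 to +1.3.

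**Dropout related to 3-week change, same pattern in both arms.** Assume logit(dropout) = −2.9 − 1.3 × standardised 3-week change. This gives 9.2% missing and raises the completers' mean 3-week change by 0.102 SD. With ρ the correlation between 3-week and 3-month change:

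bias = 0.102 × ρ × (11.2 − 3.73) = 0.102 × ρ × 7.47

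| ρ | poor responders leave | good responders leave (slope reversed) |
|---|---|---|
| 0.5 | +0.38 | −0.38 |
| 0.7 | +0.53 | −0.53 |
| 0.9 | +0.69 | −0.69 |

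This is 8 to 14% of 5 cmH2O. With SDs of 9.8 and 3.3 the factor is 6.5 and the range is 0.33 to 0.60. If exactly the lowest decile of 3-week change is lost, the shift is 0.195 SD and the bias is 0.195 × ρ × 7.47 = +0.73, +1.02 and +1.31.

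**Against the standard error.** √(11.2²/54 + 3.73²/18) = √(2.32 + 0.77) = 1.76. A bias of 0.4 to 0.7 is 0.23 to 0.40 standard errors, which moves a nominal two-sided 5% test to about 5.6 to 6.8%.

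**What the 3-week value buys.** In simulated trials of 60 and 20 patients, an arm-specific regression of 3-month change on 3-week change, averaged over all randomised patients, gave:

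- Dropout on 3-week change, either direction: remaining bias within about 0.03; standard error changed by about 1% or less.
- Lowest decile lost: remaining bias within about 0.02; standard error up to about 10% larger.
- Random dropout: no bias; standard error not increased.
- Dropout on the 3-month change itself: bias of about 0.75 reduced to 0.60, 0.37 and 0.14 for ρ = 0.5, 0.7 and 0.9, so reduced but not removed.

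**The case against.** The strongest objection is that this is a matter of silence. The article is condensed, its analysis section is three sentences, and the handling of missing values is commonly left to the full protocol or analysis plan. Imputation can precede a T test or a regression, so the test and the intention-to-treat label do not strictly contradict each other. This stands in part: no sentence says that patients are excluded, and exclusion is an inference from the named test. But the article does fix a two-time-point outcome and a test on it, and that choice leaves out a scheduled 3-week measurement which would serve the promised analysis better.

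A reader might infer that the plan overstates the effect of IMT. The article does not support that. The features that make loss plausible (hospital testing, discharge before follow-up, severe patients) concern travel and severity, not poor MIP response. If well-recovered patients skip the visit, the sign reverses with equal size; if the gap in cmH2O and the dropout rate are equal in both arms, the bias is zero.

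Two further points are fair. The bias is modest against a standard error of 1.76. And near-zero bias after adjustment is expected when dropout is simulated from the same 3-week value; the more demanding test is dropout on the 3-month value, where adjustment helps only partly. The check used an arm-specific regression, not the mixed model itself, which must estimate its covariances from about 20 controls.

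**Conclusion.** The point holds in limited form. As written and run on observed values, the T test and regression would analyse about 72 of 80 patients at the planned dropout, would be a completer analysis, and would not use the 3-week MIP. The possible distortion is about 0.4 to 0.7 cmH2O in either direction. That rests on assumed SDs of 11.2 and 3.73, correlations of 0.5 to 0.9, and about 9% dropout depending on 3-week change in the same way in both arms. It reaches about 1.3 only in the extreme cases shown. The article supports neither a stated exclusion rule nor a direction of bias. The change is worth making because a better method is available from data already planned; the trial's validity does not hinge on it.

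**What to change.** Estimate the 3-month difference in MIP for all randomised patients with a repeated-measures mixed model using baseline, 3-week and 3-month MIP. Let variances differ by arm, in keeping with the plan's threefold SD ratio. Name in advance a simpler covariance structure in case the unstructured one cannot be fitted with about 20 controls, and use small-sample degrees of freedom. The 3-week value only supplies information on patients who leave later; the endpoint stays at 3 months.

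Add one sensitivity analysis that shifts the missing 3-month values away from the missing-at-random prediction, upwards and downwards, and reports the shift at which the conclusion changes. Keep the T test on available changes if wanted, labelled a completer analysis.

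Cost: analysis-plan wording and some programming, with no new patients or measurements. Downside: the model relies on missing at random, which the sensitivity analysis probes but cannot confirm, and on covariance estimates from a small control arm.
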